#### 15.2.2.8 Study Eligibility Screener

We are developing a program to help us support better support families while their child is going through cancer therapy. May I ask you about your basic needs at home to see if you are eligible for this program?

|                                                                                                                                                         |     |    |
|---------------------------------------------------------------------------------------------------------------------------------------------------------|-----|----|
| Is your child between age 12 and 17.9 years?                                                                                                            | YES | NO |
| Has your child received at least one cycle of chemotherapy?                                                                                             |     |    |
| Are at least 2 more cycles of chemotherapy planned for your child?                                                                                      |     |    |
| Has your child reported that food tastes different to them since they started chemotherapy?                                                             |     |    |
| In the last 6 months, did you ever worry that the food would run out before you got money to buy more?                                                  |     |    |
| If you checked YES, would you like help with this?                                                                                                      |     |    |
| In the last 6 months, has your utility company (gas, electric, oil, water) sent you a letter threatening to shut off service for not paying your bills? |     |    |
| If you checked YES, would you like help with this?                                                                                                      |     |    |
| In the last 6 months was there a time when you couldn't pay the rent or mortgage in time because you didn't have the money?                             |     |    |
| If you checked YES, would you like help with this?                                                                                                      |     |    |

|                                                                                                                                                                                         |  |  |
|-----------------------------------------------------------------------------------------------------------------------------------------------------------------------------------------|--|--|
| In the last 6 months, has lack of reliable transportation stopped anyone in your family from going to medical appointments, meetings, work, or getting things needed from daily living? |  |  |
| If you checked YES, would you like help with this?                                                                                                                                      |  |  |
| Are any of your needs urgent? (for example: I don't have food for tonight, I don't have a place to sleep tonight).                                                                      |  |  |

### 15.2.2.9 Time Demands

Over the past 7 days, how much time did you or someone else in your family spend cooking dinner or supper? Please do not include time spent eating. \_\_\_\_\_ minutes total over 7 days

Please respond to each statement by marking the box that best describes you

|                                                                                            | Not at all | Little bit | Some what | Quite a bit | Very much |
|--------------------------------------------------------------------------------------------|------------|------------|-----------|-------------|-----------|
| I am satisfied with my ability to do things for my family                                  |            |            |           |             |           |
| I am satisfied with how much work I can do (including work at home)                        |            |            |           |             |           |
| I feel good about my ability to do things for my family                                    |            |            |           |             |           |
| I am satisfied with my ability to do work that is important to me (including work at home) |            |            |           |             |           |
| I am satisfied with my ability to participate in family activities                         |            |            |           |             |           |
| I am satisfied with the amount of time I spend doing work (including work at home)         |            |            |           |             |           |
| I am happy with how much I do for my family                                                |            |            |           |             |           |
| I am satisfied with my ability to work (including work at home)                            |            |            |           |             |           |
| The quality of my work is as good as I want it to be                                       |            |            |           |             |           |
| I am satisfied with my ability to do caregiving tasks.                                     |            |            |           |             |           |
| I am satisfied with my ability to meet the needs of my family                              |            |            |           |             |           |
| I am satisfied with my ability to perform my daily routines                                |            |            |           |             |           |

## 15.3 APPENDIX III – Study Semi-Structured Interview Guides

### 15.3.1 Parent Interview Guide

Thank you for taking the time to speak with me today about the MTM Kids research study, which is looking at a new way of supporting families' food-related needs during treatment. We need your feedback on what parts of MTM Kids have worked well and not so well for you over the last month. We also appreciate your advice about what you liked, did not like, and/or we should change about MTM Kids to make it better for future families. We value your input and willingness to be in this study.

I am part of the MTM Kids research team. I have no clinical involvement with the healthcare team taking care of your child. My goal for talking with you today is to find out what about MTM Kids is not working and what is working so the study team can improve MTM Kids. Nothing you share will have effects on the care your child is receiving or your ability to continue in this study.

To start, I want to get a better understanding of your experience with MTM Kids.

1. When you think about MTM Kids, what words would you use to describe it?
2. The goal of MTM Kids is to help families meet their needs for nutritious, easy to prepare food during a child's cancer treatment. From your perspective, how well is MTM Kids doing that? [SEP]**Rephrase options:** Can you describe any ways in which MTM Kids has been useful (or not useful) to you and your family? [SEP]**Probe on:** [SEP]
  - a. What changes would you like to see made to MTM Kids to make it better?
  - b. [if not mentioned] What about the number of meals per week?
3. When you think about your family's needs right now for healthy, easy to prepare food right now, can you describe how MTM Kids does and doesn't help address those needs? **Probe on:**
  - a. What specific changes would you like to see in MTM Kids to make it better?
  - b. About how often you are placing an MTM Kids order?

[If less often than weekly] What influenced your ordering meals less often than weekly? **Probe on:**

---

- a. Number of meals, meal size/portions, meal types, freezer space?
- b. How difficult or easy has it been to order meals online?

[If number of meals, portions, types, space] what ideas do you have about how we could to improve X

[If difficult] please walk me through aspects of the ordering process that were difficult for you

4. How easy or difficult was it for you to select meals that would appeal to your family?

[If difficult], Please walk me through some aspects of meal selection that were difficult for you.

**Probe on:**

- a. meal types

5. How easy or difficult was receiving meal deliveries for you?

[If difficult], Please walk me through some difficulties with meal deliveries.

6. How would you describe the overall influence that MTM Kids is having on your household's basic needs (food, transportation, utilities, housing).

7. You mentioned [insert barriers mentioned]; any other difficulties you using MTM Kids?

**Probe on:**

- a. What other factors that prevented you from getting meals when you needed them?
- b. What other factors that prevented you from using MTM Kids how you wanted?

8. Would you participate in MTM Kids again or recommend it to another family? [L][SEP] What would you say to that family?

The next questions ask about the connections you see, if any, between MTM Kids and the overall care that your child is receiving.

9. From your perspective, how valuable or not is MTM Kids in connection to clinical care for your child?

---

10. When in their child's illness do you think MTM Kids be most helpful to families? **Probe:** around diagnosis, after hospitalization, transplant, or another type of major illness-related event

11. What else do you want to say about your experience with MTM Kids and needed improvements?

Again, thank you for taking the time to speak with me today about the MTM Kids research study. We value your input and willingness to be in this study.

### 15.3.2 Adolescent Interview Guide

Thank you for talking with me today about the MTM Kids research study – that's the frozen meals being delivered to your family. We want to find ways to help kids going through chemo and their families have meals that are easy to prepare. You are in the MTM-Kids study, which is looking at a new way of helping families during treatment. We want to make the MTM program works for kids like you. We ask for your thoughts about one of the frozen meals you tried. We also ask for your advice about how to make the frozen meals better for kids and their families. We value your input and saying yes to this study.

I am part of the MTM Kids research team. I'm not a part of the team taking care of you. I am talking with you to learn what about MTM Kids is and is not working for kids going through chemo so the study team can make the meals better for kids.

1. To start, please show me or take a share a picture/show us a MTM-Kids meal you tried. **Probe on:**

[if they haven't tried any] Please tell me about why you haven't tried a meal yet. Now, please tell me about something else you ate recently.

2. How did that meal/food work for you? **Probe on:**

- a. How was the taste for you – too spicy, not spicy enough?
- b. How was the smell?
- c. How was the amount – too much, not enough?
- d. Did someone heat it up for you, or did you do it yourself?

[if by self] How was that for you?

---

3. What are your ideas about how we can make the frozen meals better for kids going through chemo? **Probe on:**

- a. More /less spice?
- b. Smaller/larger portions?
- c. Add more meal types?

[if more types] What ideas do you have about new meals or other things to eat that kids going through chemo would enjoy?

4. When you think about your family's needs right now for healthy, easy to prepare food right now, can you describe how MTM Kids does and doesn't help address those needs? **Probe on:**

- c. What specific changes would you like to see in MTM Kids to make it better?
- d. Who is ordering the MTM Kids meals?

[if the adolescent]

- a. About how often are you doing that?

[If less often than weekly] What influenced your ordering meals less often than weekly? **Probe on:**

- c. Number of meals, meal size/portions, meal types, freezer space?
- d. How difficult or easy has it been to order meals online?

[If number of meals, portions, types, space] what ideas do you have about how we could to improve X

[If difficult] please walk me through aspects of the ordering process that were difficult for you

5. How easy or difficult was it for you to select meals that would appeal to you and your family?

[If difficult], Please walk me through some aspects of meal selection that were difficult for you.

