A second pathway of risk is time demands on parents. Serious pediatric illnesses are expensive to the healthcare system; the system minimizes its costs by shifting care to outpatient settings and prompting parents to perform clinical tasks (administering medications, flushing catheters, changing dressings, monitoring vital signs, assessing and managing symptoms).[36] Parents must also meet the emotional needs of the adolescent with the diagnosis and any siblings, manage administrative components of their child's care (insurance prior authorization, medical bills, payment plans), maintain their home and communicate with providers and various agencies,[36] all while sustaining some level of employment to support their household and preserve access to employer-sponsored health insurance. These competing demands can similarly contribute to compensatory coping whereby caregivers devote time typically used for usual household tasks, such as grocery shopping and meal prep to caregiving, which affects the nutritional pathway.

Finally, the third pathway of risk is the influence of the physiological manifestations of the serious illness and its treatment on nutrition. Chemotherapy-induced alterations in taste (metallic taste in mouth) and symptoms that affect eating (nausea, vomiting, pain, fatigue, dry mouth) are common and contribute to decline in food-related enjoyment and nutritional intake. Taste alterations typically occur within the first week of treatment[40] and last six months or even years following treatment completion.[42] Parents may purchase whatever foods children in active treatment believe they will enjoy (but then the foods do not taste as expected so the adolescent will not eat them), which means less money to buy food for the household. Lengthy outpatient stays require parents to stock both their temporary lodging near the hospital and the family residence with food, which means less capacity for preparing healthy meals and cutting back on food for the household.[43] **To address inequities in household food and nutrition security and thus reduce disparities in outcomes for pediatric serious illness populations, we need rigorous evaluations of high quality, high intensity interventions that comprehensively address these three pathways.**

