The goal of this study is to conduct a single-arm study to (a) determine the feasibility of recruiting a study sample and retaining that sample through the duration of the study period (b) determine the feasibility, appropriateness and acceptability of MTM-Kids from the participants' perspectives, and (c) explore signals of change in food-related insecurities, cost coping, time demands and financial well-being. We hypothesize that for households experiencing food-related insecurities, providing healthy, frozen meals tailored to a common chemotherapy-induced taste alteration feasible, is appropriate and acceptable to children in active treatment for cancer and their parents. We will be guided by the CONSORT extension for feasibility studies.[46] Quantitative and qualitative feedback at multiple time points will enable rapid refinements of MTM-Kids and the protocol for the future efficacy trial. Our results will inform the potential for a future 2-group randomized efficacy trial with gift cards for online food delivery as the likely comparator, and later

---

cost effectiveness studies that advance our goal to extend healthcare financing models to include MTM in pediatric healthcare settings where seriously ill children receive care.

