### 4.1 Study Intervention

We will enroll 5 adolescent + 5 parents (5 dyads) in the formative test, and then 10 adolescents + 10 parents (10 dyads) in the validation test for a total of 15 adolescents and 15 parents. The sample size is based on evidence that testing with 5 users identifies 85% of barriers and facilitators to accessing program materials and putting them to use to inform refinements, and 3 iterations of feedback per user during the testing period identifies 98% [47, 48] Thus, we expect that 15 dyads total with 3 iterations of feedback via semi-structured interviews with the adolescent and also with the parent over the 12-week study period will provide sufficient data to uncover aspects of study processes and the program materials that need refinement prior to efficacy testing. For the formative and evaluative tests, we will use unique sets of dyads to gain a broader perspective than is possible with the same sets. We will also focus on children in the adolescent age group (ages 12-17.9 years) for this more in-depth data collection because they are more likely than younger children to express opinions independent of parental influence.[49]

Equiti Foods will tailor flavorings and deliver selected meals along with condiments to enable individualization by household members. The intervention will be 12-weeks duration, with weekly "doses" (meal deliveries) of up to 10 meals per week, as suggested by MTM studies with adult populations. [32, 44] Twelve weeks duration enables three iterations of feedback about the prior month's experience with MTM-Kids.

Participation will require (a) completing a survey at baseline (T1), receipt of MTM-Kids over 12 weeks, (b) participating in interviews at 4, 8, and 12 weeks (T2, T3, T4) after starting to receive meals to inform refinement, and (c) completing a follow-up survey at 12 weeks (T4). While we will not ask participants to forgo other forms of food-related assistance, we will ask them to tell us about food assistance requested and received. Interested dyads will join the informed consent/assent process, complete baseline surveys, and set up an account on Equiti Food's website where they can select/order the first MTM allotment.

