#### 15.2.1.4 Adolescent Alterations in Taste and Other Treatment-Related Symptoms

Thank you for agreeing to be in this research study. Our goal is to find ways to better support children and their families during the child's treatment with chemotherapy.

The first questions ask about taste changes some adolescents have after chemotherapy. Please click the circle that best describes how much that taste change **bothered you this week**.

|                                   | Not at all | A little | Medium | A lot | Extremely |
|-----------------------------------|------------|----------|--------|-------|-----------|
| Difficulty tasting sweet          |            |          |        |       |           |
| Difficulty tasting salty          |            |          |        |       |           |
| Difficulty tasting sour           |            |          |        |       |           |
| Difficulty tasting bitter         |            |          |        |       |           |
| Difficulty tasting flavors        |            |          |        |       |           |
| Everything tastes bad             |            |          |        |       |           |
| Food doesn't taste like it should |            |          |        |       |           |
| Bitter taste in my mouth          |            |          |        |       |           |
| Bad taste in my mouth             |            |          |        |       |           |
| Metal taste in my mouth           |            |          |        |       |           |
| Can't eat hot food                |            |          |        |       |           |

|                      |  |  |  |  |  |
|----------------------|--|--|--|--|--|
| Can't eat spicy food |  |  |  |  |  |
| Can't eat meat       |  |  |  |  |  |

Please tell us about any other taste changes that bothered you this week by writing them here:  
[insert text box]

The next questions are about other treatment-related symptoms adolescents can have. Please tell us how much each of these things **bothered you yesterday or today** by clicking the circle that best describes that amount:

|                                       | Not at all | A little | Medium | A lot | Extremely |
|---------------------------------------|------------|----------|--------|-------|-----------|
| Feeling disappointed or sad           |            |          |        |       |           |

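### The adolescent interview guide names spice as the only flavour attribute when asking how a study meal tasted, although the meals are tailored to a chemotherapy-induced taste alteration

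*Protocol*

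**What the plan says.** **What the meals are for.** The hypothesis in Protocol 1.2 concerns frozen meals "tailored to a common chemotherapy-induced taste alteration". That sentence does not name the alteration; earlier in 1.2, metallic taste is given as the example. On delivery, 4.1 states: "Equiti Foods will tailor flavorings and deliver selected meals along with condiments to enable individualization by household members".

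**What the adolescent is asked about the meal (15.3.2).**
- Question 2 opens with "How did that meal/food work for you". Its taste probe (2a) is "How was the taste for you – too spicy, not spicy enough"; the other probes cover smell, amount and who heated the meal.
- Question 3 opens with "What are your ideas about how we can make the frozen meals better for kids going through chemo". Its probes are "More /less spice", portion size and meal types.

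**What is measured alongside.** Sections 4.1 and 7.2.1 place the taste-alteration scale at the start of the interviews at weeks 4, 8 and 12. The form (15.2.1.4) has 13 items, including "Metal taste in my mouth", and a free-text box for other taste changes.

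**How the answers are used.** Section 8 plans rapid content analysis by two coders within days of each interview. Under 8.3.4, the processes and the meals are refined after 5 dyads, before the validation test. Section 8.3.3 links taste scores qualitatively to interview themes.

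**The concern.** A probe that follows a general question with two examples from one dimension invites an answer in that dimension. An adolescent whose meal tasted metallic, bitter or of nothing may not say so, or may answer in terms of spice because that is what was offered.

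This matters because the feedback is the input for changing the meals, and the first round of changes rests on few respondents. The protocol's own interest in taste is also wider than spice. Section 1.1 mentions cravings for foods high in sugar or sodium. Section 8 justifies enrolling similar numbers of girls and boys partly by the effect of sex hormones on sweet and bitter processing, and plans to explore sex in the qualitative as well as the quantitative data on taste and meal acceptability. The guide has no sweet or bitter prompt to support that.

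**Working it through.** No formula applies and no stated figure depends on this point. The check is a reading of each place where the taste of a study meal could be reported, with simple counts.

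**Step 1. Flavour probes in the adolescent guide.** There are two, 2a and 3a. Both name spice and nothing else: 2 of 2.

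**Step 2. Coverage against the study's own taste scale (15.2.1.4).** The items fall into four groups:
- difficulty tasting sweet, salty, sour, bitter, or flavours in general: 5
- food tasting bad or not as it should: 2
- bitter, bad or metallic taste in the mouth: 3
- unable to eat hot food, spicy food or meat: 3

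5 + 2 + 3 + 3 = 13. One item concerns spicy food, so 13 − 1 = 12 concern something that the flavour probes do not name. Some of these could still come out under general wording: the two food-tastes-wrong items and the flavours item under the opening words of 2a (3 items), and meat under the meal-types probe (1 item). On that generous reading 12 − 3 − 1 = 8 remain: difficulty tasting sweet, salty, sour and bitter; bitter, bad and metallic mouth taste; and hot food. The range of 8 to 12 out of 13 describes coverage. It does not measure harm, since a symptom scale and a meal interview need not match item for item.

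**Step 3. Does another instrument ask how the meal tasted?**

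| Source | What it asks | Taste of the study meal? |
|---|---|---|
| Taste scale, 15.2.1.4 | How much taste changes bothered the adolescent that week | No; general taste |
| Adolescent acceptability and appropriateness, 15.2.1.2 | Appeal and variety of choices, feeling cared for, recommendation, fit, number of meals, delivery timing, meal size | No |
| Parent interview, 15.3.1 | Usefulness, ordering, selection (probe: meal types), delivery | No |
| Adolescent interview, 2a and 3a | Taste and flavour, prompted by spice | Yes |

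The parent acceptability items under 15.2.2.3 are not visible in the text reviewed and could not be checked. Under 7.2.2 they are parent-completed scaled items, so they would not supply the adolescent's own account of a meal.

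**Step 4. Condiments.** They are part of the delivered intervention in 4.1. Neither interview guide asks whether they were used.

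**Step 5. How much feedback precedes the first refinement.** 5 dyads × 3 interviews = at most 15 adolescent interviews, from 5 adolescents. The whole study gives at most 15 × 3 = 45.

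**The case against.** The case on the other side is substantial, and most of it stands.

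- **The interview is semi-structured.** The stems of questions 2 and 3 and the closing question are open, and 2a itself begins by asking how the taste was before it gives examples. An adolescent can mention a metallic taste at any of these points to an interviewer trained in work with adolescents. A reader might infer that the guide forces a choice between two closed answers. It does not.
- **The taste scale comes first.** The respondent reaches 2a having just considered 13 taste items and a free-text box, which weakens any pull towards spice. What it does not supply is a report on the meal: it asks about taste in general that week.
- **Spice is relevant.** It is an item on the study's own scale, and the protocol never says which flavour dimension is tailored. A reader might infer that refinement is being steered to the wrong dimension. The documents do not support that: without a defined target, spice can be called incomplete but not wrong.
- **The linkage in 8.3.3 survives.** A reader might infer that taste scores would have almost nothing to be linked to. They are to be linked to interview themes generally, which can include smell, amount, meals not tried and suggested changes.
- **Condiments** are described as letting household members individualise meals, not as the vehicle for the chemotherapy tailoring. An ordinary follow-up question could establish their use.

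What remains is that the only prompts about the taste of the meal name one attribute. Open stems reduce the effect of a leading probe but are no reason to keep it.

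**Conclusion.** The point holds in a narrow form. Both flavour probes in the adolescent guide name only spice, while the meals are tailored to a chemotherapy-induced taste alteration for which metallic taste is the example given. No other instrument that could be read asks how the study meal tasted. The probe may therefore under-elicit metallic, bitter, sweet, salty, sour or bland taste in the feedback that drives refinement.

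The size is small. The point touches exploratory objective 2.3.2 and the refinement step in 8.3.4. It does not touch the primary feasibility benchmarks, the secondary acceptability scores or the sample size. The direction of any prompting bias is a judgement about question wording; the protocol contains no data on it. The conclusion assumes that interviewers use the probes roughly as written and that the unseen parent items do not ask adolescents about taste.

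**What to change.** Change the wording in 15.3.2, preferably before the formative test:

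- Replace 2a with a neutral question, such as *How did it taste to you?*, followed by balanced probes aligned to the taste scale: metallic; bitter; too or not enough salty, sweet, sour or spicy; no taste.
- Replace 3a with *What would you change about the flavour?* and the same probes.
- Optionally add one question on whether any condiments were used and whether they changed the taste.

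The cost is an edit to the guide and about one minute per interview (an estimate), so at most about 45 minutes over 45 adolescent interviews that are planned at 20 to 30 minutes each. No new procedure, visit or measure is needed.
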